#### 4.5.3 Relationship between Adverse Events and Investigational Vaccines

**Impossible:** Adverse events occur due to other factors, and there is sufficient evidence to prove that adverse reactions/events are caused by other reasons and unrelated to d vaccination.

**Unlikely:** The occurrence of adverse events may be caused by other factors, such as the clinical status of the subject, other treatments or accompanying medication, which are inconsistent with the known adverse reactions of vaccination.

**Possible:** Adverse events are consistent with known investigational vaccine information, have a reasonable temporal sequence with vaccination, and/or have occurred for vaccination. There is also a causal relationship with the investigational vaccine, but it may also be related to other factors.

**Likely:** Adverse events are consistent with the known investigational vaccine information and have causal relationship with the investigational vaccine, and cannot be explained by other factors, such as the clinical status of the subject, other treatments or concomitant medication.

**Definite:** Adverse events are consistent with the known investigational vaccine information and have a causal relationship with the investigational vaccine, and this relationship cannot be explained by other factors, such as the clinical status of the subject, other treatments or accompanying drugs. In addition, adverse events occurred repeatedly when the subjects used the investigational vaccine again.

#### 4.5.4 Adverse Event of Special Interest

According to the CIOMS VII definition, AESI refers to a class of scientific and medical events (including serious or non-serious) related to investigational vaccines or projects, which require investigators to continuously monitor and quickly communicate with the sponsor. These events need further study to understand their characteristics; Depending on the nature of the event,

the sponsor also needs to communicate quickly with other relevant parties (such as regulatory authorities).

AESI related to this vaccine include: **nervous system diseases** (generalized convulsions, Guillain-Barre syndrome, acute disseminated encephalomyelitis, aseptic meningitis, general convulsions, peripheral facial paralysis, loss of smell and taste), immune system diseases (vaccine-related respiratory diseases increase, anaphylactic shock, multisystem inflammatory syndrome in children), **respiratory diseases** (acute respiratory distress syndrome), **cardiac system diseases** (acute cardiovascular injury (including myocarditis, pericarditis, arrhythmia, heart failure, myocardial infarction), blood system damage (thrombocytopenia, coagulation dysfunction (including coagulation diseases, thrombosis, thromboembolism, internal/external bleeding, stroke)), **kidney system diseases** (acute kidney injury), liver system diseases (acute liver injury) and **skin system diseases** (chilblain-like lesions, single organ skin vasculitis, erythema multiforme, alopecia). The follow-up period of AESI is 6 months after the full course of immunization.

## **4.6 Randomization and Blinding**

### **4.6.1 Randomization**

Stratified block randomization method will be employed in the study to perform stratifications according to sequential vaccination time (1-3 months, 4-6 months, and  $\geq 6$  months after 2 doses). Interactive Web Response System (IWRS) will be used in subject randomization and vaccine allocation.

The randomization statistician will produce subject randomization list and vaccine randomization list by SAS 9.4 (or later version), which will be imported into IWRS by system engineer. After one subject is screened successfully, the investigator at each center will log onto IWRS to get randomization number of the subject. Before vaccination, the investigator will receive the vaccine number from IWRS and inoculate vaccines accordingly. If the vaccine is damaged, the investigator could acquire a new vaccine number from IWRS and inoculate the vaccine with new vaccine number.

### **4.6.2 Blinding**

Before the start of the study, the staffs from sponsor who will not participate in the clinical trial will blind the vaccines to be used in the study together with the unblinded randomization statistician. The vaccine label will be stucked on the specified position of each vaccine according to vaccine randomization list. The randomization statistician will supervise and guide the process of blinding. After blinding is completed, the vaccine randomization list will be sealed by the unblind randomization statistician. The whole blinding process will be recorded and written in a

document named blinding records, which is one of the important documents of this trial. The blinding personnel cannot participate in other related works of the trial, and they are not allowed to tell any information to any personnel who participates in the trial.

The subject randomization list and vaccine randomization list will be sealed, including randomization number, vaccine number and the corresponding group assignment, together with the randomization seed number. They will be well sealed and saved until the database is locked.

#### **4.6.3 Emergency Blind Code Breaking**

In an emergency, when the investigator thinks that the group assignment information of one subject is beneficial for the handling of adverse events, it will be broken through the Emergency Blind Code Breaking Module in IWRS. The investigators need to discuss with the Sponsor and both shall reach agreement before performing emergency blind code breaking.

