## **8. SAFETY DEFINITION, REPORTING AND MONITORING**

### **8.1 General Precautions**

This clinical trial is a randomized, double-blind and controlled trial design.

Before the start of the trial, the sponsor shall strictly examine the trial site in accordance with GCP requirements, focusing on whether the environmental facilities of the trial site meet the requirements of "Vaccination Management Standards" and "Guiding Principles for Quality Management of Vaccine Clinical Trials". Ensure the first aid facilities and first aid equipment in the first aid room are complete and effective, and the first aid doctors have corresponding qualifications and capabilities. Emergency related personnel (emergency doctors, emergency nurses, ambulance drivers, etc.) are trained to be qualified and familiar with the transfer routes and procedures of the agreed hospital. They are on standby at the trial site during vaccination. The trial site shall be equipped with ambulances. The ambulance shall be parked in a fixed position to keep the vehicle in good condition and in an emergency and shall be under the command and transfer of the emergency response team at any time. During the vaccination period, the agreement hospital will make daily preparations for medical personnel, instruments and equipment, first aid drugs and first aid sites to ensure that the subjects can receive timely treatment. The trial site shall formulate an emergency plan, stipulate personnel responsibilities, contact numbers, rescue routes and other measures to ensure timely handling of unexpected adverse events, and ensure effective contact between subjects and investigators so that any adverse events can be reported and handled quickly.

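### Emergency code breaking requires prior sponsor agreement, with no provision for urgency, disagreement or an unreachable sponsor

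*Protocol*

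**What the plan says.** Section 4.6.3 (Emergency Blind Code Breaking) has two sentences. The first gives the trigger and the tool: "In an emergency, when the investigator thinks that the group assignment information of one subject is beneficial for the handling of adverse events", and then "it will be broken through the Emergency Blind Code Breaking Module in IWRS". The second sets a condition that must be met first: "The investigators need to discuss with the Sponsor and both shall reach agreement before performing emergency blind code breaking".

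Section 4.6.2 (Blinding) covers custody of the code. Of the subject and vaccine randomization lists it says: "They will be well sealed and saved until the database is locked". It also bars the personnel who did the blinding from other work on the trial and from passing information to anyone who takes part in it.

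Section 8.1 (General Precautions) states the level of blinding: "This clinical trial is a randomized, double-blind and controlled trial design".

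**The concern.** The second sentence of Section 4.6.3 asks for consent, not for notification. The investigator's judgement starts the process but cannot complete it within the protocol. The situations covered are by definition emergencies in which the investigator already thinks the assignment would help, and in those the time needed to reach a sponsor representative and settle the matter may count.

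Two things are at stake. The first is timely access to the assignment for the single subject concerned. The second is the conduct of the blind: each request brings the sponsor into a discussion about one subject's adverse event and into the decision to unblind that subject.

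Who may break the code is a conduct rule that belongs in the protocol. This protocol states one, so the point does not concern a detail left to a statistical analysis plan.

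**Working it through.** No arithmetic applies. The rule involves no alpha, power, effect size, margin or dropout rate. The check is whether any other part of the protocol softens it.

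1. **Is agreement a precondition?** Yes. Section 4.6.3 requires it before the break and requires it of both parties. It names no urgent exception, time limit or sponsor contact, and says nothing about what follows if the two disagree.

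2. **Is there another route to the assignment?** None is described. Section 4.6.2 keeps the lists sealed until database lock. Section 6.2 says the boxes look alike and carry only the vaccine number, so the packaging is not meant to reveal the vaccine. Before lock, the IWRS module is the only route described, and the condition governs it. Section 9 puts lock after the Day 28 antibody results and at least one month of safety follow-up.

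3. **Do the emergency and safety sections relax the condition?** No.
   - Section 8.1 requires emergency staff, an ambulance, an agreed hospital and an emergency plan, but does not mention the code.
   - Section 8.3 requires the investigator to act at once on a serious adverse event and to report it to the sponsor within 24 hours. It does not mention code breaking.
   - Sections 5.1.4 and 7.6 (suspension and termination) and 7.3.1 (safety observation, including a face-to-face visit within 24 hours for events of Grade 3 or above) do not mention it either.

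4. **Does treatment depend on the code?** No. Section 8.3 requires appropriate measures for a serious adverse event without reference to assignment. Section 7.5 allows necessary medication and medical care for adverse events. Section 6.4 provides for one study dose, so no later study dose depends on knowing the group. What may be delayed is knowledge of the assignment.

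5. **Is the sponsor drawn into the decision?** Yes. Section 4.6.3 makes it one of the two parties that must agree. Because Section 4.6.2 excludes the blinding personnel from other trial work, the sponsor representative who agrees would ordinarily come from the side of the sponsor that runs the trial. That last step is an inference, since Section 4.6.3 names no role.

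6. **Does it reach the primary analysis?** Not materially. The primary endpoints in Section 4.3.1 are laboratory neutralizing antibody results (GMT and 4-fold rise at 14 and 28 days). Nothing in Section 10 depends on how codes are broken.

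**The case against.** The best defence is that this is a deliberate restriction. A sponsor may want a second opinion before a code is broken, because unnecessary breaks erode the blind. Emergency care proceeds in any case. No part of the protocol requires the investigator to have sole authority, and the protocol identifies no adverse event whose handling differs by vaccine. Few subjects are likely to be involved.

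Most of this stands, and it limits the size of the point. It does not answer the gap: a rule written for emergencies has no outcome when the sponsor is unreachable or disagrees. The wish for a second opinion can be met by consultation that is not a condition.

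A reader might infer more than the text supports in five ways:

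- **That the two sentences of Section 4.6.3 contradict each other.** They do not. One gives a trigger and the other a precondition, which together form a single restrictive procedure.
- **That the IWRS module is locked without the sponsor.** The protocol describes no technical block. It sets a procedural duty, so a break without agreement would be non-compliant but is not shown to be impossible.
- **That the sponsor learns the assignment.** Agreeing to a break is not the same as being told the result, and Section 4.6.3 does not say who receives it. Involvement in the decision is supported; unblinding of the sponsor is not.
- **That a subject's treatment waits on sponsor consent.** Sections 7.5, 8.1 and 8.3 provide care independently of the code.
- **That the sponsor's links to the makers of both vaccines bias the decision.** Those links show no direction of bias.

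**Conclusion.** The point holds as a defect in a stated rule. Section 4.6.3 makes emergency code breaking conditional on prior sponsor agreement, and no section provides for urgency, disagreement or an unreachable sponsor. Followed as written, it can delay or prevent protocol-compliant access to the assignment when the investigator judges it useful. It also makes the sponsor a party to a subject-level unblinding decision in a double-blind trial.

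The extent is small. The consequence falls on single cases, treatment is not held up by the rule, and sample size, power and type I error are untouched. The sponsor should make the change, but the trial's conclusions do not turn on it.

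This rests on two assumptions. The protocol gives no expected number of code breaks, so that there will be few is a judgement. It also does not list which sponsor staff are blinded; the point takes the double-blind statement in Section 8.1 to cover those who run the trial.

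**What to change.** Replace the second sentence of Section 4.6.3 with wording to this effect:

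- The investigator may break the code in IWRS for the subject concerned. Where time allows, the investigator consults the sponsor first, but the sponsor's agreement is not a condition.
- The investigator then promptly notifies the sponsor that a break has occurred, giving the date, subject number and reason. The assignment is not disclosed to blinded sponsor staff.
- Each break is documented. Sections 4.6.1 to 4.6.3 describe no log of code breaks, so the text should say where the record is kept, for instance in IWRS if the system supports it.

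The change concerns who may open the code and who is told. It leaves every dose and treatment rule as it stands.

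The cost is a short edit to one section, a documentation requirement, and slightly less sponsor control over unnecessary breaks. The sponsor can still review each break afterwards from the notification. Sites already use IWRS directly for randomization (Section 4.6.1) and already report serious adverse events to the sponsor within 24 hours (Section 8.3), so the added burden should be light.

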### **5. SCREENING AND WITHDRAWAL OF SUBJECTS**

The subjects must fulfill all eligibility criteria to be involved in this study. No exemptions from any in-/exclusion criteria will be allowed. If any deviation from eligibility is retrospectively detected for an already randomized subject, the investigator and sponsor must determine immediately the safety to treat this subject further within the study.

#### **5.1 Subject Population**

##### **5.1.1 Inclusion Criteria**

- Age range: populations aged 18 years and above;
- Judged by the investigator that the health condition is well after inquiry and physical examination;
- Vaccinated with 2 doses of CNBG inactivated COVID-19 vaccine according to the product insert;
- Female subjects who are not nursing or pregnant at the time of enrolment (negative urine pregnancy test) and have no family planning within the first 6 months after enrollment. Effective contraceptive measures have been taken within 2 weeks before inclusion.
- During the whole follow-up period of the study, be able and willing to complete the whole prescribed study plan;
- With self ability to understand the study procedures, the informed consent & voluntarily sign an informed consent form and is able to comply with the requirements of the clinical study protocol.

##### **5.1.2 Exclusion Criteria**

- Confirmed cases, suspected cases or asymptomatic cases of COVID-19;

- With a history of SARS and MERS infection (self-report, on-site inquiry);
- Has vaccinated with any other vaccines rather than one or more doses of Sinopharm CNBG inactivated COVID-19 vaccine;
- Axillary temperature  $\geq 37.3$  °C (forehead temperature  $\geq 37.8$  °C);
- Previous severe allergic reactions to vaccination (such as acute allergic reactions, urticaria, dyspnea, angioneurotic edema or abdominal pain)
- Allergy to known components of recombinant COVID-19 vaccine (e.g., aluminum and histidine);
- Severe respiratory diseases, severe liver and kidney diseases, hypertension (systolic blood pressure  $\geq 150$  mmHg, diastolic blood pressure  $\geq 90$  mmHg), diabetic complications, malignant tumors, various acute diseases or acute attacks of chronic diseases;
- Has been diagnosed with congenital or acquired immunodeficiency, HIV infection, lymphoma, leukemia or other autoimmune diseases;
- Has a history of convulsions, epilepsy, encephalopathy, long-term alcohol and drug abuse, history of thyroidectomy, history of infectious diseases, mental illness or family history (direct);
- With Congenital malformation or developmental disorder, genetic defect, severe malnutrition, etc.;
- Has a history of coagulation dysfunction (e.g. coagulation factors deficiency and coagulation diseases);
- Asplenia or splenectomy, functional asplenia caused by any situation;
- Receiving anti-TB (tuberculosis) therapy;
- Received immunoenhancement or inhibitor therapy within 3 months (continuous oral or IV administration for more than 14 days);
- Received other vaccines within 14 days before vaccination;
- Received blood products within 3 months before vaccination;
- Received other investigational drugs within 6 months before vaccination;
- Plans to move before the end of the study or leave the local area for a long time during the scheduled study visits;
- Other circumstances judged by investigators that are not suitable for this clinical trial.

### **5.1.3 Criteria for Early Withdrawal from the Trial**

Early withdrawal means that the subjects fail to complete vaccination and blood collection

according to the protocol, and the investigators decide whether to continue the follow-up research according to the situation. In any of the following situations, the subject will withdraw from the clinical trial in advance.

- Subjects asked to withdraw from clinical trials;
- Intolerable adverse events, whether related to the investigational drug or not
- The health status of the subjects does not allow them to continue to participate in this trial.
- Subjects are vaccinated with other investigational vaccines during the study period.
- Any reasons the investigator deems necessary.

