|                                                      | 
 
- Other circumstances judged by investigators that are not suitable for this clinical trial.
 
                                                                                                                                                                                                                                                                                                                                                                                                                                                                                                                                                                                                                                                                                                                                                                                                                                                                                                                     |
| Subject's early withdrawal                    | 
Early withdrawal means that the subject fails to complete the vaccination and blood collection procedures in accordance with clinical study protocol, and investigator decides whether to continue the follow-up related research according to the situation. When any of the following conditions occur, the subject will withdraw from the clinical trial in advance.
 
 
- The subject requests to withdraw from the clinical trial;
 
- Intolerable adverse events, whether related to the investigational drug or not;
 
- The health status of the subjects does not allow them to continue to participate in this trial;
 
- The subjects are vaccinated with other clinical investigational vaccines during the study period;
 
- Any other reason that investigator considers.
 
                                                                                                                                                                                    |

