## **6.4 Administration and Immunization Schedule**

Route of Administration: lateral deltoid muscle of either upper arm, intramuscular injection.

Vaccination Procedure: Among the population who had completed two doses of inactivated COVID-19 vaccines according to the 0 and 21 days (+7 days) immunization schedule, one dose of recombinant COVID-19 vaccine (CHO cells) or inactivated COVID-19 vaccines (Vero cells) will be inoculated at different time points of 1~3 months, 4~6 months, and  $\geq 6$  months for sequential immunization

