## **7.3 Safety Observation and Follow-up**

### **7.3.1 Safety Observation**

(1) Observe the site for 30 minutes after vaccination to collect local and systemic adverse events.

(2) Telephone follow-up once in 6-24 hours after vaccination, within 1-3 days and 4-7 days respectively, the subjects were followed-up by telephone and guided to observe the adverse events

correctly and fill in the diary card.

(3) On the 14th day (Visit 4), the investigator reviews the filling of the diary card during this period and re-collect the diary card.

(4) On the 8th -30th day after vaccination, the investigator uses telephone follow-up once a week, combined with active report of the subjects to monitor the safety.

(5) When it is known that the subject has adverse reactions/events of Grade 3 or above, a face-to-face visit should take place within 24 hours.

(6) SAEs and AESIs are observed from the first dose to 6 months after the full course of vaccination by means of monthly telephone follow-up and self-reports from the subjects.

Note: Subjects should report respiratory tract infection symptoms such as fever and cough. Investigators should make comprehensive judgments, carefully identify whether it is common solicitation symptoms after vaccination or infection caused by other reasons, and closely observe the disease progress. Once the disease worsens, report it to the person in charge of the site quickly, and start the green treatment channel quickly to ensure that the subjects get timely diagnosis and treatment.

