### **(2) Reporting Procedures for Serious Adverse Events**

- Reporting procedures of investigators

Any serious adverse event, whether or not related to the investigational vaccine, the

investigator must submit the initial report of the "Serious Adverse Event Report Form" to the drug administration department, the sponsor and the ethics committee by fax, e-mail or EDC system or personal delivery within 24 hours after learning about it.

Subsequently, the follow-up report of the "Serious Adverse Event Report Form" shall be submitted regularly until the end of the event. All information is reported in the "Serious Adverse Event Report Form" in the form of written reports, including description of adverse reactions/events, onset time and type, duration, intensity, causal relationship with vaccination, results, treatment methods (symptomatic treatment) and other relevant clinical and laboratory data.

When receiving the report of serious adverse events/reactions, the investigator shall, together with the sponsor, comprehensively consider the duration, scope, intensity, outcome and the willingness of the subject to decide whether the subject should continue to participate in the study or withdraw from the study in advance.

- Reporting procedure of sponsors

During the clinical trial of drugs, sponsors need to quickly report unexpected and serious adverse reactions (SUSAR) that are definitely related to or suspicious of the tested drugs in the form of case-by-case safety reports according to the Standards and Procedures for Rapid Reporting of Safety Data during Clinical Trial of Drugs. If the researcher and the sponsor cannot reach an agreement on the judgment of the causal relationship between adverse events and drugs, either party's judgment cannot exclude those related to the test drugs, and the sponsor should also make a quick report.

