#### **10.7 Handling of Missing Data**

In FAS immunogenicity analysis, LOCF (Last Observation Carried Forward) method will be used to impute the missing values in antibody data after vaccination. And other

immunogenicity endpoints will be derived from the imputed data. The missing data in safety and immunogenicity persistence evaluation will be not imputed.

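### With one study injection, withdrawal for adverse events or health stops no dose, and the protocol leaves later SAE/AESI collection in those subjects to the investigator despite a 6-month safety endpoint

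*Protocol*

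**What the plan says.** **One dose.** Section 6.4 provides that "one dose of recombinant COVID-19 vaccine (CHO cells) or inactivated COVID-19 vaccines (Vero cells) will be inoculated" at one of three intervals after the primary course. Table 4 places vaccination at V1 (D0) only.

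**Withdrawal.** Section 5.1.3 states: "In any of the following situations, the subject will withdraw from the clinical trial in advance". The list includes "Intolerable adverse events, whether related to the investigational drug or not" and "The health status of the subjects does not allow them to continue to participate in this trial", as well as the subject's request, receipt of another investigational vaccine, and any reason the investigator considers necessary. The sentence just before the list defines early withdrawal as not completing vaccination and blood collection. It gives the investigator the choice about later follow-up; in the Synopsis row on early withdrawal the wording is "investigator decides whether to continue the follow-up related research according to the situation".

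**After an SAE.** Under the reporting procedures in section 8.3, investigator and sponsor together "decide whether the subject should continue to participate in the study or withdraw from the study in advance".

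**Required observation.** Section 7.3.1 says "SAEs and AESIs are observed from the first dose to 6 months after the full course of vaccination", by monthly calls and self-report. The Synopsis safety endpoint is SAE and AESI incidence to 6 months, and section 4.5.4 sets the same AESI period. Section 7.8 describes site closure as coming after all subjects have had 6 months of safety observation and 12 months of blood collection.

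**Analysis.** The Safety Set in section 10.2 is everyone who received the dose. Section 10.7 says "The missing data in safety and immunogenicity persistence evaluation will be not imputed".

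**The concern.** In a multi-dose trial, a rule that takes a subject out after an intolerable reaction mainly prevents the next dose. Here there is no next dose. What a withdrawal after D0 can end is observation and sampling.

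The triggers select people who reacted badly or became ill, so their later outcomes are unlikely to resemble those of the subjects who stay. If follow-up stops, a later new SAE or AESI goes unseen while the subject remains in the denominator. Because the choice rests with each investigator, the loss can differ by site. If the two vaccines differ in how often they lead to withdrawal, it can also differ by arm.

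The remaining blood samples are exposed too. A subject who leaves before the day 14 draw has no post-dose titre and so drops out of the Per-Protocol Set. In the Full Analysis Set, last observation carried forward, read literally, would have only the pre-dose titre to carry.

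An analysis plan cannot recover data that were never collected, so the matter belongs in the protocol.

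**Working it through.** **1. Is there a study dose left to stop?** No. Section 6.4 and Table 4 give one injection, at D0.

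**2. Is leaving mandatory, and does leaving end follow-up?** The passages do not agree.
- Section 5.1.3 and the Synopsis make withdrawal mandatory in the listed situations, but leave continued follow-up to the investigator.
- Section 8.3 makes continuing or withdrawing after an SAE a joint, case-by-case decision.
- The Synopsis endpoint and sections 4.5.4, 7.3.1 and 7.8 set 6 months of observation with no exception for withdrawn subjects, and section 7.8 speaks of all subjects.
- No section says that the monthly calls continue after withdrawal.

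**3. What is still captured after withdrawal?**
- The event that triggered it, which has already been recorded.
- Reactions persisting within days 0-30, recorded until relieved (section 7.3.2).
- Known SAEs, followed until they disappear or stabilise, with outcome (section 8.3).

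Not assured are a new SAE or AESI that starts later and the remaining scheduled samples.

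**4. How does the analysis treat the gap?** Section 10.3.4 reports subjects and percentages by group and compares them by Fisher's exact test. With a Safety Set of everyone dosed and no imputation, an event that was not observed is not counted.

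**5. Size.** The protocol states no rate of withdrawal for adverse events or health and no SAE rate, so there is no figure of its own to reproduce. The 15-20% drop-out in section 10.1 is an all-cause allowance in the immunogenicity sample size and cannot stand in.

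Illustration by assumption: a fraction w of an arm is withdrawn with follow-up stopped, and these subjects have k times the later event risk of the rest. The share of the arm's later events that is missed is wk / (1 - w + wk).

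| w | k | Calculation | Share missed |
|---|---|---|---|
| 2% | 1 | 0.02 / (0.98 + 0.02) | 2% |
| 2% | 3 | 0.06 / (0.98 + 0.06) | 6% |
| 5% | 1 | 0.05 / (0.95 + 0.05) | 5% |
| 5% | 3 | 0.15 / (0.95 + 0.15) | 14% |

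In subject counts, with 900 per arm and an assumed 1% later risk in those who stay, the number missed is 900 × w × k × 0.01. This runs from 900 × 0.02 × 1 × 0.01 = 0.18 to 900 × 0.05 × 3 × 0.01 = 1.35 subjects per arm.

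The result depends heavily on the assumed later risk. Take 9 observed SAE subjects (1% of 900), 2% withdrawn, and 10% of those having a later first SAE. Then 900 × 0.02 × 0.10 = 1.8 are missed, which is 1.8 / 10.8 = 17% of the true count. With observed risk 0.5-2%, withdrawal 0.5-5% and later first-SAE risk 2-10%, the share runs from 0.09 / 18.09 = 0.5% to 4.5 / 9.0 = 50%. If the investigator continues follow-up, the loss is zero.

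**The case against.** The strongest reply is that section 5.1.3 does not itself end safety follow-up. It ties early withdrawal to vaccination and blood collection and expressly allows follow-up to continue. Section 8.3 does not force anyone out after an SAE, and section 7.8 presupposes complete 6-month observation. That stands, and it rules out several stronger readings that a reader might infer.

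- **That these subjects must leave observation and the 6-month endpoint is emptied.** The discretion clause and section 8.3 contradict this. The triggering event is on record, known SAEs are followed, and the subjects stay in the Safety Set.
- **That severe COVID-19 cases and deaths disappear through health-status withdrawal.** A hospitalised case is already an SAE under section 8.3 and must be followed. Death is a listed outcome in section 8.4, and section 7.4 provides separate sampling for cases. Only an episode that begins after follow-up has stopped could be missed.
- **That a difference in reactogenicity is hidden.** The 30-minute observation, the 0-7 day diary and the early calls record an intolerable reaction before it can lead to withdrawal.
- **That 6-month incidence is understated by the percentages in the table.** Events before withdrawal stay in the numerator, and a second SAE in a subject already counted changes no subject-level incidence. The percentages apply to later events only.
- **That the whole 15-20% drop-out is of this kind.** Section 10.1 does not split it by cause.

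It is also fair to say that the analysis of incomplete follow-up may be set out in an SAP that is not shown. Whether the data are collected at all is a protocol matter. Discretion permits the calls to continue but does not require it, and so does not close the gap.

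**Conclusion.** The point holds in a limited form. The mandatory withdrawal wording conflicts with its own discretion clause, with the case-by-case decision in section 8.3, and with the 6-month SAE/AESI observation. As written, collection of later new SAEs and AESIs, and of the remaining samples, is optional in the subjects whose later safety matters most. Any loss is informative and may vary by site or arm.

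Its size cannot be computed from the documents. It is zero if investigators continue follow-up. It is about 2-14% of an arm's later events if 2-5% are withdrawn with all follow-up stopped and carry 1-3 times the later risk; both inputs are assumptions. With few SAEs expected, even one or two missed subjects per arm could be noticeable. This is a worthwhile, low-cost correction. It does not show that the safety endpoint is invalid.

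**What to change.** Reconcile the Synopsis row on early withdrawal, section 5.1.3 and the post-SAE decision in section 8.3 with the Synopsis safety endpoint and sections 4.5.4, 7.3.1 and 7.8. In doing so, separate stopping study procedures from stopping data collection:

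- After the injection, SAE/AESI data collection continues to 6 months through the monthly calls already planned, unless the subject withdraws consent or is lost to follow-up.
- Scheduled blood draws continue where the subject agrees and is able.
- Titres taken after another investigational vaccine are flagged and kept out of the Per-Protocol and Immunogenicity Persistence Sets. Section 10.2 does not expressly exclude them, although section 7.7 lists such vaccination as a protocol violation.
- The reason for withdrawal is recorded.

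Decisions on the subject's clinical management stay with the investigator; the change concerns data collection only.

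The cost is an amendment, a matching sentence in the consent form, and a few more calls and draws in subjects who might otherwise have left. The calls and visits are already in the schedule.
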